## **5.9 Special Ocular Examinations**

### **Visual acuity testing**

With the appropriate corrective lenses based on that subject’s refraction, the best corrected visual acuity (BCVA) will be measured using a Logarithmic visual acuity chart or according to local routine practice. The subject’s presenting visual acuity without refraction will also be evaluated. Visual acuity will be obtained prior to pupil dilation. Data will be transformed into LogMAR score.

### **Tonometry**

Intraocular pressure for both eyes will be measured using a non-contact tonometry. Tonometry should be performed prior to pupil dilation.

### **Slit-lamp biomicroscopy**

A standard ophthalmic examination using slit lamp biomicroscopy will be performed in both eyes by the unmasked Primary Treating Ophthalmologist. The Anterior chamber cell count will be measured during the examination according to the SUN criteria (see Appendix I), which should be performed prior to pupil dilation.

### **Ophthalmoscopy**

Ophthalmoscopy will be performed by the Primary Treating Ophthalmologist under the dilation of the pupil to determine both vitreous haze grading and the absence/presence of active chorioretinal and/or retinal vascular lesions. Grading of vitreous haze will be based on the publication from the National Eye Institute (NEI)

which has also been adapted by the SUN working group (see Appendix II).

### **Fundus photography**

Fundus photography will be performed to obtain evidence of the absence/presence of active chorioretinal and/or retinal vascular lesions.

### **Optical coherence tomography (OCT)**

Optical coherence tomography will be used to determine the absence/presence of retinal lesions and macular alternations.

### **Fundus fluorescence angiography (FFA)**

Fundus fluorescence angiography will be performed to determine the absence/presence of active chorioretinal and/or retinal vascular lesions.

## **5.10 Study Schedule Overview**

|                                            | Screenin
g/Baselin
e | Month 1
(phone
call) | Month 2
(phone
call) | Month 3
(in
person) | End trial
month
after
Month 3
(phone
call) | Post-sym
ptom
visit (our
study
site or
local
hospital) | Unsched
uled visit
(in
person) |
|--------------------------------------------|----------------------------|----------------------------|----------------------------|---------------------------|-----------------------------------------------------------|--------------------------------------------------------------------------|-----------------------------------------|
| Visit window (day)                         | 0                          | ±7                         | ±7                         | ±14                       | ±7                                                        | -                                                                        | -                                       |
| Written informed consent                   | ×                          |                            |                            |                           |                                                           |                                                                          |                                         |
| Inclusion/exclusion criteria               | ×                          |                            |                            |                           |                                                           |                                                                          |                                         |
| Randomization                              | ×                          |                            |                            |                           |                                                           |                                                                          |                                         |
| General information and medical history    | ×                          |                            |                            |                           |                                                           |                                                                          |                                         |
| Answer to Questions (Module 1 or Module 2) |                            | ×                          | ×                          | ×                         | ×                                                         |                                                                          | ×                                       |
| Visual acuity testing                      | ×                          |                            |                            | ×                         |                                                           | ×                                                                        | ×                                       |
| Slit-lamp biomicroscopy                    | ×                          |                            |                            | ×                         |                                                           | ×                                                                        | ×                                       |
| Ophthalmoscopy                             | ×                          |                            |                            | ×                         |                                                           | ×                                                                        | ×                                       |
| Any other necessary                        | ×                          |                            |                            | ×                         |                                                           | ×                                                                        | ×                                       |

|                                           |   | Screenin
g/Basel
in
e | Month 1
(phone
call) | Month 2
(phone
call) | Month 3
(in
person) | End trial
month
after
Month 3
(phone
call) | Post-sym
ptom
visit (our
study
site or
local
hospital) | Unsched
uled visit
(in
person) |
|-------------------------------------------|---|--------------------------------|----------------------------|----------------------------|---------------------------|-----------------------------------------------------------|--------------------------------------------------------------------------|-----------------------------------------|
| Visit window
(day)                     |   | 0                              | ±7                         | ±7                         | ±14                       | ±7                                                        | -                                                                        | -                                       |
| auxiliary
examination at
discretion |   |                                |                            |                            |                           |                                                           |                                                                          |                                         |
| Treatment,
prescription and
record  | × |                                |                            |                            | ×                         |                                                           | ×                                                                        | ×                                       |
| Adverse event
evaluation               |   |                                | ×                          | ×                          | ×                         | ×                                                         | ×                                                                        | ×                                       |

\* can be assessed by phone call.

## 6 Outcome Assessments

### 6.1 Adjudication Committee

An adjudication committee who are unaware of group assignment will independently determine each endpoint event.

### 6.2 Primary Outcome

The primary outcome will be the time to symptomatic worsening over the course of 3 months of follow-up.

**Symptomatic worsening is defined if one of following newly onset symptoms occurs in at least one eye lasting for at least 2 days: eye redness, eye pain, decreased vision, light sensitivity or floaters.**

### 6.3 Secondary Outcomes

- a. Time to clinically-confirmed uveitis worsening.

**Clinically-confirmed uveitis worsening is defined if any of the following criteria are met in at least one eye: new active, inflammatory chorioretinal or retinal vascular lesions (determined by clinical examination such as ophthalmoscopy or ancillary testing such as fundus photography and fluorescein angiography); worsening of best corrected visual acuity by 0.3 LogMAR score or more; a two-step increase in anterior chamber cell grade relative to baseline; or a two-step increase in vitreous haze grade relative to baseline. A 2-step increase is represented by a change of grade 0 to grade 2+; or grade 0.5+ to grade 3+.**

- b. Proportion of each reason for symptomatic uveitis worsening.
- c. Proportion of symptomatic uveitis worsening.
- d. Proportion of each reason for clinically-confirmed uveitis worsening.

- e. Time to initiation of step-up treatment.

**Step-up treatment is defined if any of the following criteria are met: addition of another systemic immunosuppressive agent (or biologics), switching to another systemic immunosuppressive agent (or biologics), or increasing doses of any currently systemically administered drugs.**

- f. Time to treatment interruptions.

**Treatment interruptions are defined if any of the following criteria are met: decreasing doses of or discontinuing any currently systemically administered drugs due to adverse events rather than disease improvement.**

- g. Time to hospitalization for any reasons.
- h. Time to hospitalization for ocular disease.
- i. Time to laboratory-confirmed COVID-19.
- j. Patient adherence, defined as proportion correctly vaccinated for at least one dose or maintaining not vaccinated per protocol throughout the trial.
- k. Proportion of vaccinated type and dose.
- l. Proportion of uveitis remission throughout the trial.

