### 4.1 Inclusion Criteria

A subject will be eligible for study participation if she/he meets all of the following inclusion criteria:

- a. Aged 12 years or older
- b. Not yet vaccinated prior to the Screening.
- c. Diagnosed with any forms of uveitis in any eye.
- d. An **inactive disease** status (all the following criteria are met):
  - (1) **Anterior chamber cells of 0.5+ or less (See SUN criteria in Appendix I);**
  - (2) **Vitreous haze of 0.5+ or less (See NEI/SUN criteria in Appendix II);**
  - (3) **No active inflammatory choroidal or retinal vascular lesions.**

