### 4.2 Exclusion Criteria

The presence of any of the following will exclude a subject from the study enrollment:

- a. Complete uveitis remission: Inactive disease for 3 months after discontinuing all treatments for eye disease.
- b. Any known vaccine contraindications according to manufactures' instructions:
  - (1) Individuals with a history of anaphylaxis to any component of the vaccine;
  - (2) Individuals with a body temperature over 38.5°C;
  - (3) Pregnancy.

- c. Any other condition which, in the opinion of the Investigator, would put the subject at risk by participation in the protocol.

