#### **5.4 Baseline Assessments**

The Baseline visit becomes time-point zero from which all other visit dates are calculated. The Screening and the Baseline can be performed on the same day. Considering the pragmatic study design, to ensure a rapid enrollment and data collection for a broad range of participants, baseline clinical characteristics and medical history can be either reported by patients or retrieved by means of a study site-specific query of the health record. Pre-specific baseline data include the date of

birth, gender, ethnic group, height, weight, presence of hypertension, diabetes, coronary heart disease, malignancies, type of uveitis (anterior, intermediate, posterior or panuveitis), specific uveitis diagnosis, affected eye (right, left or both), duration of uveitis, number of flares in the past 12 month, best corrected visual acuity logMAR score, and intraocular pressure.

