**Uveitis remission is defined as an inactive disease for 3 months after discontinuing all treatments for eye disease.**

- m. Vaccine inaccessibility, defined as proportion having gone to the vaccination site but refused due to the lack of vaccines, whereby this situation continues until the end of trial.
- n. Reasons for not yet vaccinated until the end of trial among those who should have been vaccinated per protocol.
- o. Change in anterior chamber cells from the Baseline to the end of three months.

- p. Change in vitreous haze from the Baseline to the end of three months.
- q. Change in best corrected visual acuity LogMAR score from the Baseline to the end of three months.

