## **3.2 Secondary and Safety Outcomes**

- a. Time to clinically-confirmed uveitis worsening.

Clinically-confirmed uveitis worsening is defined if any of the following criteria are met in at least one eye: new active, inflammatory chorioretinal or retinal vascular lesions (determined by clinical examination such as ophthalmoscopy or ancillary testing such as fundus photography and fluorescein angiography); worsening of best corrected visual acuity by 0.3 LogMAR score or more; a two-step increase in anterior chamber cell grade relative to baseline; or a two-step increase in vitreous haze grade relative to baseline. *A 2-step increase is represented by a change of grade 0 to grade 2+; or grade 0.5+ to grade 3+.*

- b. Proportion of each reason for symptomatic uveitis worsening.
- c. Proportion of symptomatic uveitis worsening.
- d. Proportion of each reason for clinically-confirmed uveitis worsening.
- e. Time to initiation of step-up treatment.

Step-up treatment is defined if any of the following criteria are met: addition of another systemic immunosuppressive agent (or biologics), switching to another systemic immunosuppressive agent (or biologics), or increasing doses of any currently systemically administered drugs.

- f. Time to treatment interruptions.

Treatment interruptions are defined if any of the following criteria are met: decreasing doses of or discontinuing any currently systemically administered drugs due to adverse events rather than disease improvement.

- g. Time to hospitalization for any reasons.
- h. Time to hospitalization for ocular disease.
- i. Time to laboratory-confirmed COVID-19.
- j. Patient adherence, defined as proportion correctly vaccinated for at least one dose or maintaining not vaccinated per protocol throughout the trial.

k. Proportion of vaccinated type and dose.

l. Proportion of uveitis remission throughout the trial.

Uveitis remission is defined as an inactive disease for 3 months after discontinuing all treatments for eye disease.

m. Vaccine inaccessibility, defined as proportion having gone to the vaccination site but refused due to the lack of vaccines, whereby this situation continues until the end of trial.

n. Reasons for not yet vaccinated until the end of trial among those who should have been vaccinated per protocol.

o. Change in anterior chamber cells from the Baseline to the end of three months.

p. Change in vitreous haze from the Baseline to the end of three months.

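### Step-up and treatment-interruption outcomes count dose changes of drugs not given for uveitis, leave a first systemic agent unclear, and never capture escalation by local treatment alone

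*Supplement*

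**What the plan says.** Protocol 2.3 names treatment interruptions and initiation of step-up treatment among the secondary objectives. Section 6.3 e defines step-up by three routes: "addition of another systemic immunosuppressive agent (or biologics), switching to another systemic immunosuppressive agent (or biologics), or increasing doses of any currently systemically administered drugs". Section 6.3 f defines an interruption as "decreasing doses of or discontinuing any currently systemically administered drugs due to adverse events rather than disease improvement".

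SAP 3.2 e and f repeat both definitions without refinement, including "or increasing doses of any currently systemically administered drugs" for step-up and "discontinuing any currently systemically administered drugs due to adverse events rather than disease improvement" for interruption. SAP 11.2 analyses each with univariate Cox regression. SAP 11.1 makes all secondary outcomes descriptive, reported as point estimates with unadjusted 95% confidence intervals.

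Three other places bear on the point:
- Protocol 4.1 admits patients "Diagnosed with any forms of uveitis in any eye" and requires no systemic treatment at entry.
- Protocol 5.4 records "presence of hypertension, diabetes, coronary heart disease, malignancies" at baseline.
- The remission definition in 6.3 l refers to disease that stays inactive "after discontinuing all treatments for eye disease". That wording is specific to the eye and covers any route.

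**The concern.** The names of e and f suggest that they track escalation and interruption of uveitis treatment. The wording does something different in three respects.

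1. **Indication.** The dose-change routes apply to every systemic drug the patient takes, whatever it is for.
2. **First agent.** A patient on drops only, or on no treatment for less than 3 months, can enter. If that patient starts a first systemic agent, the text does not settle whether it counts as adding *another* one.
3. **Route.** A flare handled by local treatment alone is invisible to e.

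Both outcomes will be reported as hazard ratios with confidence intervals. Readers will take those ratios as statements about uveitis treatment. No other listed outcome measures drug escalation or dose reduction: hospitalization (g, h) picks up severe cases and remission (l) only completed withdrawal. The treating ophthalmologist is unmasked (protocol 5.3), so a fair description of background treatment by arm is worth having.

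**Working it through.** The documents state no rate, power or sample size for e or f, so there is no planned figure to reproduce. The main check applies the text to cases.

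| Case | Counted as step-up (e)? | Counted as interruption (f)? |
|---|---|---|
| Dose of a blood-pressure or diabetes drug raised | Yes: third route, no indication limit | – |
| Such a drug cut because of an adverse event | – | Yes |
| First systemic immunosuppressive or biologic in a patient on none | Unclear: depends on the reading of *another* | – |
| Systemic anti-infective started for infectious uveitis | No route fits | – |
| Drops or a local injection started or intensified, nothing else | No | – |
| Uveitis drug reduced because of a vaccine adverse event | – | Yes |
| Uveitis drug reduced for a reason other than an adverse event or improvement | – | No |

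On the fourth case, protocol 1.1 says infectious uveitis needs anti-infection therapy. Raising the dose of a current anti-infective would count; starting one would not.

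**Illustration of unrelated events.** The 657 per arm comes from protocol 9.1. The 10% deferred-arm rate and hazard ratio of 1.5 are borrowed from the primary outcome as stand-ins for step-up; 5% is an alternative rate. The share of patients with an unrelated dose increase, equal in both arms, is assumed at 2%, 5% or 10%. Hazards are constant and there is no dropout.

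- Cumulative hazard: h = −ln(1 − p). For p = 0.10, h1 = 0.1054 and h2 = 1.5 × 0.1054 = 0.1580.
- Unrelated hazard q: −ln(0.98) = 0.0202; −ln(0.95) = 0.0513; −ln(0.90) = 0.1054.
- Observed ratio = (h2 + q) / (h1 + q).

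| Deferred-arm step-up | 2% unrelated | 5% unrelated | 10% unrelated |
|---|---|---|---|
| 10% | 0.1782/0.1256 = 1.42 | 0.2093/0.1567 = 1.34 | 0.2634/0.2107 = 1.25 |
| 5% (h1 = 0.0513, h2 = 0.0769) | 1.36 | 1.25 | 1.16 |

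The unrelated events also add to the event count. The interval becomes narrower while its centre moves towards 1.

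**Illustration of missed events.** With nothing missed, expected events are 657 × (0.100 + 0.146) = 162. Suppose 30% of true step-ups are missed equally in both arms. The hazards become 0.7 × 0.1054 = 0.0738 and 1.5 × 0.0738 = 0.1106, so the ratio stays 1.5. Events fall to 657 × (0.0711 + 0.1047) = 116, and the interval on the log scale widens by √(162/116) = 1.18. Equal omission costs precision; it biases the ratio only if it differs by arm.

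**The case against.** The best defence is that a systemic-only step-up is a legitimate, harder endpoint. Protocol 1.1 says most non-infectious uveitis is treated mainly with immunosuppressive agents. A flare treated locally can still register in the primary outcome, in clinically confirmed worsening, and in outcomes o to q if present at Month 3. The add, switch or increase rule also needs no judgement about reasons. An all-route endpoint tied to worsening would depend on reasons recorded by the unmasked ophthalmologist. This stands, and it is why outcome e should stay systemic. It does not defend counting drugs for other conditions.

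A reader might infer more than the documents support:

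- **That a first systemic drug is certainly missed.** *Another* can also mean any newly added agent, and protocol 1.1 lists steroids among immunosuppressants. This is an ambiguity that the adjudication committee has no written rule to settle.
- **That reductions caused by vaccination are missed.** Those due to a vaccine adverse event count under f. Only precautionary or planned reductions fall outside, and no passage says these occur.
- **That stops made to reach remission are recorded nowhere.** Completed withdrawal ending in remission is outcome l, and tapering in quiet disease may be the improvement that f deliberately excludes.
- **That the loss can be counted.** If half of 162 events led to more treatment (81) and 30 to 60% of those were local only, 24 to 49 would be uncounted. Neither share is in the documents, and 162 ignores the planned 15% dropout.

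**Conclusion.** Two defects follow from the plain text. Dose changes of systemic drugs unrelated to uveitis count in both e and f, and local-only escalation never counts in e. A third, the status of a first systemic agent, is an ambiguity to resolve.

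Unrelated events equal in both arms pull the hazard ratio towards 1; the illustration runs from 1.42 down to 1.16 for an assumed true ratio of 1.5. Equality is itself an assumption. For f in particular, adverse-event-driven cuts of other drugs could differ by arm. The actual size and direction therefore cannot be derived from the documents.

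It would be wrong to conclude that the trial's main comparison is compromised. The primary outcome and sample size do not use these definitions, and SAP 11.1 says that no inferences can be drawn from secondary outcomes. The change is worth making because the rule as written misclassifies events and is cheap to correct.

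**What to change.** In protocol 6.3 e and f and SAP 3.2 e and f:

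1. Limit both outcomes to systemic drugs given for uveitis, and say how a drug given for both the eye and an associated systemic disease is classed.
2. State that starting a first systemic agent for uveitis (immunosuppressive, biologic or anti-infective) counts as step-up.
3. Keep this systemic definition as outcome e.
4. In SAP 11.2, add a descriptive summary by arm of local treatment escalation, and of reductions of uveitis treatment not due to adverse events, with the reason where recorded.

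The source exists. Protocol 5.10 collects treatment and prescriptions at baseline, Month 3, post-symptom and unscheduled visits, and 5.6 requires local hospitals to return the prescription.

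The cost is some extra abstraction of records. Reasons may be incomplete or written by unmasked staff, so they belong in the descriptive summary. No treatment record is taken at the Month 1 and Month 2 calls, so changes between visits may be dated imprecisely.
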